### Trial advisory committee

An advisory committee has been formed to support this project. The role of the advisory committee will be to: 1) monitor and supervise progress of the trial; 2) support recruitment by engaging with clients and patients through their networks; 3) review, at regular intervals, relevant information about the study; 4) provide feedback to consider how study findings can be presented and used in the future; 5) inform the development and execution of an integrated knowledge mobilization plan.

Due to the low risk of the trial intervention, there will not be a formal data safety and monitoring board, as approved by the governing research ethics board.

## Data analysis

### Sample size justification

The primary outcome is a continuous quantity measured using the PCL-5. The sample size is calculated to have 80% power at 5% type I error. Data from a previous waitlist control study of SKY gives us data to calculate an appropriate sample size. A study by Seppälä et al. used the PCL-M (a DSM-IV version of the PCL-5) for their primary outcome measures [29]. With a conservative standard deviation of magnitude 11 and an effect size of 5, 76 participants must be recruited in each group. A conservative dropout rate of 25% is projected for this study, which has been observed in other clinical trials for PTSD [4, 57]. Accounting for this expected dropout rate, 200 participants will be recruited, with 100 in each group.

### Effectiveness

The primary outcome (PCL-5) will be measured at baseline, 6-weeks, 12-weeks and 30 weeks. The distribution of PCL-5 scores will be examined and an appropriate transformation to correct the possible non-normality will be applied if required. Repeated measures analysis of variance will be used to compare the active intervention and WLC groups at T2, T3, and T4 while adjusting for baseline measures. The demographic characteristics, including age, sex, gender, and baseline symptom severity will be compared between intervention and control groups and the comparison of the primary outcome will be adjusted for significant confounders that may be identified over the course of the study. If significant, this will be included in the repeated measures analysis of variance for adjustment. Descriptive and exploratory statistics will be used to describe and compare the exploratory outcomes (depression, anxiety, pain, and quality of life) between intervention and control groups [58]. This will be an intention-to-treat analysis, where all participants who are randomized will be included in the analysis. There are no pre-planned subgroup analyses.

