#### Primary objectives

*Effectiveness evaluation*. In Canadian veterans with clinically significant PTSD symptoms, we will estimate the short-term (6-weeks) effectiveness of v-SKY compared to a waitlist control at reducing PTSD symptoms as measured by PTSD Checklist for DSM-5 (PCL-5).

*Implementation evaluation*. We will explore adoption of v-SKY by examining the intervention’s acceptability, accessibility, and perceived effects amongst Canadian veterans with PTSD and amongst health professionals, and administrators that work with Canadian veterans.

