#### Exploratory objectives

We will estimate the short- and long-term effects of v-SKY on quality of life, depression, anxiety, and chronic pain in Canadian veterans affected by PTSD. In addition, we will evaluate the reach, adoption, implementation, and maintenance of the v-SKY intervention amongst Canadian veterans with PTSD, SKY instructors, and the health professionals, and administrators that work with veterans.

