**Fig 1 pone.0275774.g001:**
[figure not shown]
Flowchart showing the timeline of the randomized controlled trial.

This study was originally conceived as a comparative effectiveness study using a non-inferiority approach, similar to the US study described by Mathersul et al [37, 46]. This proposed trial would have compared virtually-delivered SKY (v-SKY) to virtually-delivered cognitive processing therapy (CPT) in a non-inferiority trial, with the key innovation being virtual delivery of SKY. However, formal consultation with experts in veteran mental health care and veterans who have lived experience with PTSD indicated that the SKY intervention would likely be most useful in a Canadian context if it were to be integrated into the current treatment environment instead of being compared to a standard of care treatment. For instance, many patients in specialty clinics have not responded to existing treatments, which emphasized a need for more complementary therapeutic options. These discussions also identified wait times for access to care between 4–8 weeks, which is comparable to the wait list control time period. Likewise, as per our earlier estimates, a high number of veterans with PTSD may not be actively receiving treatment for their illness. Thus, a wait list control design was considered as the most appropriate, relevant, and feasible.

Several RCTs of SKY for veterans living with PTSD have been conducted using waitlist control designs including in the United States [29] and Australia [38]. Using a waitlist control design encompasses using a control group that is not actively receiving treatment for their illness during the intervention period. Baseline assessments will be conducted with the active intervention (ACT) and waitlist control (WLC) groups before the active intervention group receives the intervention. After the 6-week intervention period for the ACT group, there will be a 2-week data collection period for both the ACT and WLC groups. After this 2-week period, the WLC group will begin the intervention for 6-weeks and the ACT group will not. After the WLC group’s 6-week intervention, there will also be a 2-week data collection period for both groups.

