#### Outcome measures and assessments

For the effectiveness trial, change in PTSD symptoms is the primary outcome measure (**Table 4**). Changes in depressive, pain, anxiety symptoms and quality of life are exploratory outcome measures.

**Table 4 pone.0275774.t004:** Primary and exploratory outcome measures for the effectiveness evaluation.

Outcome Measure	Explanation
Change in PTSD symptoms *Primary*: Change in PCL-5 scores from baseline to post-treatment (6-weeks).	The PCL-5 is a well-validated, widely used, and easy to administer 20-item self-report scale that is widely used in PTSD research and clinical practice [47]. Responses to each item relate to the four symptom clusters for PTSD, for which separate scores can be measured and used for additional analyses. The PCL-5 will be used for follow-up assessments over the CAPS-5 because of the feasibility of a self-report measure over a semi-structured interview and to reduce the reporting burden on participants.
*Exploratory*: Prolonged changes in PCL-5 scores from baseline to 12-week follow-up and 30-week follow-up.	
Change in depressive symptoms *Exploratory*: Change in depressive symptoms as measured by the nine-item Patient Health Questionnaire (PHQ-9) scores from baseline to 6-weeks, 12-weeks, and 30-weeks follow-ups.	PHQ-9 is a well-validated and widely used self-report scale used in depression research. Each item is rated on a 4-point scale for how much it bothered the participant in the past 2 weeks. A self-report scale is more feasible than an assessor-rated scale (e.g. HAM-D17) given the virtual nature of this study.
Change in pain symptoms *Exploratory*: Change in pain symptoms as measured by the Brief Pain Inventory (BPI) from baseline to 6-weeks, 12-weeks, and 30-weeks follow-ups.	BPI is a validated self-report scale used in pain trials and clinical pain practice and is a core outcome measure per the Initiative on Methods, Measurement, and Pain Assessment in Clinical Trials (IMMPACT) recommendations [50]. Two independent and clinically relevant measures are included: pain severity and pain interference with function.

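### The PCL-5 analysis spans T2, T3 and T4 without naming the week-6 contrast as the primary test, although the waitlist arm receives SKY after T2

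*Protocol article*

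**What the plan says.** The Primary objectives section sets the question at one time point: "we will estimate the short-term (6-weeks) effectiveness of v-SKY compared to a waitlist control". Table 4 (Outcome measures and assessments) agrees. It defines the primary outcome as PCL-5 change from baseline to 6 weeks and lists as exploratory "Prolonged changes in PCL-5 scores from baseline to 12-week follow-up and 30-week follow-up". The Sample size justification rests on one two-group difference: "With a conservative standard deviation of magnitude 11 and an effect size of 5, 76 participants must be recruited in each group".

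The Trial design section describes the waitlist arm's crossover once the T2 data have been collected: "After this 2-week period, the WLC group will begin the intervention for 6-weeks and the ACT group will not".

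The Effectiveness section under Data analysis then gives the only inferential method for PCL-5: "Repeated measures analysis of variance will be used to compare the active intervention and WLC groups at T2, T3, and T4", with adjustment for baseline. It does not rank the three visits, does not say which model term carries the primary test, and does not mention that the WLC arm is no longer untreated at T3 and T4.

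For the other outcomes, the Exploratory objectives section says: "We will estimate the short- and long-term effects of v-SKY on quality of life, depression, anxiety, and chronic pain".

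**The concern.** Only T2 compares SKY with no SKY. At T3 and T4 the comparison is between participants who started SKY early and participants who started it later. A repeated-measures ANOVA over the three visits offers two standard tests, and neither answers the week-6 question. The group effect averages one controlled contrast with two post-crossover contrasts. The group-by-time test asks whether the difference between arms changes over the visits.

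If SKY helps the WLC arm too, the arms converge after T2. The averaged group effect then shrinks, and a real week-6 benefit could be missed. A small difference at T3 or T4 could also be misread as loss of benefit when the control arm has simply been treated. Because the section does not say which term is primary, the choice could be made after the data are seen.

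**Working it through.** **Inputs from the protocol article.** Difference 5 points, SD 11, 80% power, 5% type I error, 25% dropout, 100 recruited per arm (Sample size justification). The WLC arm starts SKY after T2 (Trial design).

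**Assumptions, not in the document.** The test is two-sided. The SD is 11 at every visit. The correlation ρ between any two of T2, T3 and T4 is 0.4 to 0.8. The between-arm differences at T2, T3, T4 are (5, 0, 0) for full WLC catch-up or (5, 2.5, 2.5) for half catch-up. No extra credit is given for baseline adjustment.

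**1. The plan's own figure.** n = 2 × (1.96 + 0.84)² × 11² / 5² = 75.98, so 76 per arm. This reproduces the stated number, so the trial is sized for a contrast at a single time point. With 25% dropout, 100 per arm leaves 75.

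**2. T2 contrast, 75 per arm.** SE = 11 × √(2/75) = 1.796 and 5/1.796 = 2.78. Power of the two-sided t-test is 79%.

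**3. Group effect averaged over T2–T4.** The effect is d̄ = (d₂ + d₃ + d₄)/3. The SD of a participant's three-visit mean is 11 × √((1 + 2ρ)/3), which is 8.52 at ρ = 0.4 and 10.24 at ρ = 0.8. The SE is that SD × √(2/75), which is 1.39 and 1.67.
- Full catch-up: d̄ = 5/3 = 1.67. The ratio to the SE is 1.20 and 1.00, so power is 22% and 17%.
- Half catch-up: d̄ = 10/3 = 3.33. The ratio is 2.40 and 1.99, so power is 66% and 51%.

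**4. Group-by-time test.** Noncentrality λ = (75/2) × Σ(dₖ − d̄)² / (121 × (1 − ρ)), chi-square on 2 df.
- Full catch-up: Σ = 16.67. λ = 8.6 and 25.8, so power is 75% and over 99%.
- Half catch-up: Σ = 4.17. λ = 2.2 and 6.5, so power is 24% and 62%.

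| Test | Full catch-up (5, 0, 0) | Half catch-up (5, 2.5, 2.5) |
|---|---|---|
| T2 contrast | 79% | 79% |
| Group effect over T2–T4 | 17–22% | 51–66% |
| Group-by-time | 75% to over 99% | 24–62% |

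**5. Where T3 falls.** In the Trial design text, the ACT course takes 6 weeks, data collection 2 weeks and the WLC course 6 weeks: 6 + 2 + 6 = 14. Table 1 places the WLC course in weeks 6–12 and T3 at week 12. On the first schedule the WLC arm is still in its course at week 12, and on the second it has just finished. On either schedule it is not untreated.

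**The case against.** The strongest reply is that the sentence compares the arms at three listed visits, which can be read as visit-specific comparisons from one model. A T2 comparison obtained that way is not diluted. The objective, the outcome table and the sample size all point to week 6, and an analysis plan that is not shown may settle the matter. This stands to the extent that the intended test may well be the right one. It does not remove the problem: the section itself fixes a model and a set of visits, and even on the visit-specific reading it lists three unranked comparisons, two of them after crossover.

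A reader might infer more than the text supports, in four ways.

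- **That the primary effect is certainly diluted.** It is diluted only if the all-visit group effect is the test, and the text does not say so. The size also depends on the WLC arm benefiting: with differences of (5, 5, 5) and ρ = 0.5, averaging would raise power to about 93%.
- **That an effective treatment would come out null under any standard test.** Under full catch-up the group-by-time test is well powered or close to it, at 75% to over 99%.
- **That the protocol claims a controlled 30-week effect.** Weeks 12 and 30 are exploratory, the Table 4 wording concerns change from baseline, and the exploratory objective names no comparator. The loss of an untreated control is an openly described feature of the waitlist design.
- **That T3 and T4 must be removed.** Early versus delayed start is a legitimate randomised comparison when it is labelled as such.

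**Conclusion.** The point holds as a mismatch between a week-6 primary question and an analysis statement that covers three visits without naming the week-6 contrast. Depending on which term is tested, the same trial has between 17% and over 99% power across the scenarios examined, against 79% for the T2 contrast that the sample size supports. Those figures rest on assumed correlations and assumed WLC catch-up. The direction of the dilution, given an all-visit group test and a WLC arm that benefits, does not depend on the particular values. The sample size itself is not at fault.

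The wording on long-term and prolonged effects, and the timing of T3, need clarifying so that later results are not read as SKY against no treatment.

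**What to change.** 1. In the Effectiveness section, state that the single confirmatory test is the baseline-adjusted ACT–WLC contrast in PCL-5 at T2, two-sided at 5%, from ANCOVA or as the T2 contrast of an arm-by-visit mixed model.
2. Keep T3 and T4 as exploratory. Label between-arm results there as early- versus delayed-start, and other results as within-arm change.
3. Reword the exploratory objective and the Table 4 entry so that neither can be read as SKY against an untreated control at weeks 12 and 30.
4. Reconcile the Trial design schedule with the week-12 T3 visit in Table 1, and state what T3 represents for the WLC arm.

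The cost is wording only. Sample size, visits and procedures do not change. The primary test should be fixed before unblinded outcome data are seen.

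### Repeated-measures ANOVA over T2, T3 and T4, in its classical form, cannot deliver the promised intention-to-treat analysis and ties the 6-week result to attendance at weeks 12 and 30

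*Protocol article*

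**What the plan says.** All references are to the protocol article.

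- **Method** (Data analysis, Effectiveness): "Repeated measures analysis of variance will be used to compare the active intervention and WLC groups at T2, T3, and T4". Baseline values are adjusted for. On the visits, that section says: "The primary outcome (PCL-5) will be measured at baseline, 6-weeks, 12-weeks and 30 weeks".
- **Population** (same section): "This will be an intention-to-treat analysis, where all participants who are randomized will be included in the analysis".
- **Primary endpoint** (Primary objectives; Table 4): the PCL-5 change from baseline to 6 weeks only. The 12- and 30-week changes are exploratory.
- **Expected loss** (Sample size justification): "A conservative dropout rate of 25% is projected for this study". The text does not say by which visit.
- **Withdrawals** (Data management and confidentiality): data gathered before a participant withdraws stay in use unless the participant asks otherwise, and nothing is gathered afterwards.

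**The concern.** Classical repeated-measures ANOVA works on participants with a value at every modelled visit. Used that way here, it turns the promised analysis of everyone randomised into an analysis of those who attended weeks 6, 12 and 30. It also sets aside scores that the withdrawal rule says will be kept.

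The primary question concerns week 6 alone. With T3 and T4 in the same complete-case model, a participant with a valid 6-week PCL-5 who misses week 30 leaves the primary comparison. After T2 the arms are in different situations: the active arm has finished its course and the waitlist arm is about to start. Later loss could therefore plausibly depend on how a participant was doing at T2, and do so differently by arm. At stake are an avoidable bias in the primary estimate and a completer result reported as intention-to-treat.

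**Working it through.** **Inputs.** From Sample size justification: difference 5, SD 11, power 80%, type I error 5% (taken as two-sided, which reproduces the plan's figure), 76 per group, 25% dropout, 100 per group. Timing of dropout and its dependence on outcome are my assumptions, shown as ranges.

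**1. The plan's own figure.** n = 2 × SD² × (1.960 + 0.842)² / difference² = 2 × 121 × 7.849 / 25 = 75.98, so 76 per group, as stated. Inflating for dropout, 76 / 0.75 = 101.3, or 102 per group; the plan uses 100. After 25% loss, 100 × 0.75 = 75 per arm.

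**2. Reading A: 25% is the total loss by week 30.** A complete-case analysis keeps 75 per arm, 150 of 200. If a fraction d is lost before T2, then 100(1 − d) per arm have a T2 score, and 2 × [100(1 − d) − 75] people with a T2 score are discarded. Power = Φ(5 / (11√(2/n)) − 1.960), for an unadjusted two-group comparison.

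| Lost before T2 | T2 scores per arm | Discarded despite a T2 score | Power, all T2 data | Power, completers (75 per arm) |
|---|---|---|---|---|
| 0% | 100 | 50 | 89.5% | 79.5% |
| 5% | 95 | 40 | 88.0% | 79.5% |
| 10% | 90 | 30 | 86.2% | 79.5% |
| 15% | 85 | 20 | 84.2% | 79.5% |
| 20% | 80 | 10 | 82.0% | 79.5% |
| 25% | 75 | 0 | 79.5% | 79.5% |

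Using the t distribution instead, power at 75 per arm is 79.0%.

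**3. Reading B: 25% is already lost by T2.** If a further 5-20% of the rest leave later, 71.25 down to 60 per arm are complete. About 58 to 80 of 200 are then excluded, about 8 to 30 of them with a T2 score, and power is 77.4% down to 70.2%.

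**4. Possible bias under reading A.** Assume T2 scores are normal with SD 11, the true difference is 5.0, loss before T2 is random, and the comparison is unadjusted. After T2, a share q = 1 − 0.75/(1 − d) of those with a T2 score leave. In the affected arm, P(leave) = 1/(1 + exp(−(a + b·z))), where z is the standardised T2 score (higher is worse) and a is set so that the average is q. Loss in the other arm is random. The mean of z among stayers, times 11, is the amount by which that arm's completers look better than the whole arm. The completer difference is 5 plus this shift if the active arm is affected, and 5 minus it if the waitlist arm is.

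| Lost before T2 | q | Log-odds b per SD | Shift | Active arm only | Waitlist arm only |
|---|---|---|---|---|---|
| 0% | 0.250 | 0.25 | 0.68 | 5.68 | 4.32 |
| 0% | 0.250 | 0.5 | 1.31 | 6.31 | 3.69 |
| 0% | 0.250 | 1 | 2.35 | 7.35 | 2.65 |
| 10% | 0.167 | 0.25 | 0.45 | 5.45 | 4.55 |
| 10% | 0.167 | 0.5 | 0.89 | 5.89 | 4.11 |
| 10% | 0.167 | 1 | 1.61 | 6.61 | 3.39 |
| 20% | 0.0625 | 0.25 | 0.17 | 5.17 | 4.83 |
| 20% | 0.0625 | 0.5 | 0.34 | 5.34 | 4.66 |
| 20% | 0.0625 | 1 | 0.64 | 5.64 | 4.36 |

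With the same b and q in both arms the shifts cancel and the difference stays 5.0. Using all T2 scores also gives 5.0 in every row, but only because loss before T2 was assumed random.

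**The case against.** The article gives no estimation method and no rule for missing visits. Some authors use the name repeated-measures ANOVA for a likelihood-based model that keeps partial data, and imputation would also let everyone in. Both the intention-to-treat sentence and the withdrawal rule point to an intention to use all data. Missing-data detail commonly sits in an analysis plan, which is not shown.

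Much of this stands, and it rules out four stronger readings that a reader might infer:

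- **That the two statements can never both hold.** They conflict only for the classical form without imputation.
- **That a quarter of participants will certainly be lost, including people with the 6-week endpoint.** The 25% is a projection with no visit attached. If all of it falls before T2, nobody with a T2 score is discarded.
- **That the trial becomes underpowered.** The sample was already inflated for 25% loss. Power falls clearly below target only under reading B, where further loss follows.
- **That the benefit will be exaggerated.** The direction depends on which arm has outcome-dependent loss, and equal mechanisms cancel.

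The objection does not remove the point. Silence on imputation is not the complaint. The method the article does name, read in its ordinary sense, does not fit the population it names. An analysis plan that follows the name literally repeats the conflict, and one that uses a mixed model departs from the published wording.

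**Conclusion.** The point holds in conditional form. Fitted classically and without imputation, the named analysis gives a completer result on about 150 of 200 participants if 25% is the total loss by week 30. That contradicts the intention-to-treat statement and the rule on data from withdrawals, and it makes the 6-week result depend on later attendance.

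On that reading of the 25%, 0 to 50 people with a T2 score are discarded, or 10 to 40 if 5-20% leave before T2. The power cost is modest: 79% against 82-88%. What matters more is possible bias. For log-odds of 0.25 to 1 per SD in one arm, the completer difference runs from about 5.2 to 7.4 (active arm) or about 2.6 to 4.8 (waitlist arm) against 5.0, with little or none if both arms behave alike. These are scenarios, not forecasts; the documents give no information on how dropout relates to outcome. Because this is the primary analysis and the repair is nearly free, it should be settled before data are analysed.

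**What to change.** Replace the ANOVA with a likelihood-based (REML) mixed model for repeated measures, with arm-by-visit effects and baseline PCL-5, using every available PCL-5 score from randomised participants. Name the T2 arm contrast from that model as the primary result. Such a model handles loss after T2 that depends on the observed T2 score.

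It does not settle T2 scores that are missing for reasons related to their unseen values, so add one sensitivity analysis for these; its form can be left to the SAP. State how participants with no post-baseline score are handled, and say which visit the 25% refers to.

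Cost: protocol and SAP wording and slightly more analysis work. No new data, visits or participants.
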